##### Pilot Outcomes

Participants who spend an extended amount of time in the VR-GMI program will report lower PLP incidence as well as (for individuals who have already experienced PLP onset) lower intensity and interference. These predictions are in line with previous research investigating prophylactic PLP treatment through mirror therapy in the postoperative period [23].

##### Exploratory Outcomes

The research team will explore reasons for rejecting participation as well as session or study withdrawal. The research team will also investigate whether acceptability, engagement, or PLP incidence and intensity vary according to baseline, sociodemographic, and exploratory variables (such as anxiety, depression, amputation indication, etc).

#### Recruitment

The research team aims to recruit 30 participants, 5 (17%) of whom we expect to drop out and 25 (83%) to complete the program. This sample size is in line with previous pilot studies for PLP treatments that precede RCTs [38] and suits the descriptive and exploratory aims of the study. This sample size also has 80% power to detect the desired recruitment criterion [53].

Potential participants will be approached according to the recruitment strategies and eligibility criteria outlined and recommended in phase 3, with 3 exceptions to help mitigate recruitment barriers faced in the previous phase. First, clinical resource nurses on units where LLAs are treated at the HSC will be called each week to ascertain where eligible patients are to increase the recruitment rate. Second, individuals with bilateral amputations will also be eligible for recruitment, given preliminary data from phase 3 suggesting this may be feasible. Third, patients will be eligible to participate for up to 2 months following their LLA, in line with the literature that suggests such a time frame is suitable for the administration of acute PLP intervention [20].

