#### Data Analysis

Objectives 1, 2, and 4 will be evaluated descriptively via bar graphs, means, and SDs to compare each objective across administration settings and VR stage according to preset feasibility criteria. Preset feasibility criteria must be met to determine if the VR program is acceptable (mean Theoretical Framework of Acceptability Questionnaire score >3, which indicates a more favorable acceptability rating than no opinion; Sekhon et al [54]), tolerable (at least 70% of the participants do not report any pre- or post-NRS score increases of ≥3 for PLP, RLP, or nausea), and engaging (mean session duration ≥20 min). Similar progression criteria [52] must be met to determine whether procedural feasibility is appropriate for an RCT, including recruitment (at least 50% of the patients at the HSC who appear to meet the eligibility criteria will be screened through the established pathways), retention (at least 70% of the participants who live in Winnipeg will continue to participate in the study for as long as they are able to), and attrition (at least 80% of the participants will respond at the 1-month follow-up period following their final session) rate criteria. The sample will also be compared to the population of all people who underwent an LLA at the HSC during the recruitment period (from June 2024 to March 2025) via administrative chart review to evaluate whether the characteristics are relatively proportional to one another.

For objective 3, scatterplots will be generated to explore the association between the length of program engagement and the Brief Pain Inventory or Patient Reported Outcomes Measurement Information System pain interference. Mean or median difference in length of program engagement between participants who have and have not yet experienced PLP onset will also be calculated. If appropriate, exploratory regression models will be used to examine the effect of VR dosage on PLP outcomes.

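### The 80% power claimed for 30 participants refers to a recruitment criterion whose denominator is apparently eligible hospital patients, and for which the article plans only a descriptive comparison

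*Protocol article*

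**What the plan says.** The Phase 4A Recruitment section sets the size: "The research team aims to recruit 30 participants", "5 (17%) of whom we expect to drop out and 25 (83%) to complete the program". It gives three reasons. The number matches earlier pilot studies, it "suits the descriptive and exploratory aims of the study", and, with a citation, "This sample size also has 80% power to detect the desired recruitment criterion".

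The Phase 4A Data Analysis section defines the criterion: "recruitment (at least 50% of the patients at the HSC who appear to meet the eligibility criteria will be screened through the established pathways". It is one of three procedural criteria, with retention (70% of participants who live in Winnipeg) and response at 1 month (80% of participants). Of these three the section says: "Similar progression criteria [52] must be met to determine whether procedural feasibility is appropriate for an RCT".

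On analysis, the same section states: "Objectives 1, 2, and 4 will be evaluated descriptively via bar graphs, means, and SDs". The objectives are not numbered where they are listed. Procedural feasibility is second in that list, so it is taken here as objective 2.

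**The concern.** Power is the probability that a stated decision rule succeeds when a stated true value holds, given the number of units on which the rule is computed. The article attaches it to 30 enrolled people. The recruitment criterion is computed on a different group, the hospital's apparently eligible patients. Enrolled participants have all come through screening, so within the 30 the criterion is satisfied by construction and carries no information.

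This is the only statistical performance figure offered for the sample size, and the procedural criteria decide whether the programme moves to an RCT. A reader could take from the sentence an assurance about the recruitment criterion that 30 enrolments do not supply. The same reader is told nothing about how imprecise the criteria that do rest on the participants will be.

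**Working it through.** **1. Units, side by side**

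| Item | Counted on | Source |
|---|---|---|
| Sample size carrying the 80% | 30 enrolled (25 expected to complete) | Phase 4A, Recruitment |
| Recruitment criterion, numerator | patients screened through the pathways | Phase 4A, Data Analysis |
| Recruitment criterion, denominator | HSC patients who appear eligible | Phase 4A, Data Analysis |
| Progress to March 2025 | 101 screened, 15 recruited | Results |

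The 101 are screened patients, so they bear on the numerator; the article gives no count of apparently eligible patients. Reading the criterion as recruited over eligible, or recruited over screened, does not help, because the 30 would then be the numerator.

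**2. Trying to reproduce the 80%**

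It cannot be derived from the article, which states no alpha and only one of the two rates needed (50%). As a trial only, take n = 30 as the denominator and use the exact binomial tail

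P(X ≥ r | n, p) = Σ C(n,k) p^k (1−p)^(n−k), for k = r to n,

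with r the smallest count whose tail under the null does not exceed alpha. Alpha and the second rate are assumptions.

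| Null | One-sided alpha | r | Actual size | Power at n = 30 |
|---|---|---|---|---|
| 50% | 0.05 | 20 | 0.049 | 0.29 at 60%; 0.51 at 65%; 0.73 at 70%; 0.80 at about 72% |
| 50% | 0.025 | 21 | 0.021 | 0.18 at 60%; 0.59 at 70%; 0.80 at about 75% |
| 25% | 0.05 or 0.025 | 13 | 0.022 | 0.82 at 50% |
| 30% | 0.05 | 14 | 0.040 | 0.71 at 50% |
| 40% | 0.05 | 17 | 0.048 | 0.29 at 50% |

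The bare rule of an observed share of at least 50% (15 or more of 30) passes with probability 0.57 when the true share is exactly 50%.

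So 80% is attainable at n = 30 for some pairs of rates. None of these pairs is stated, and all use the wrong unit.

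**3. The criterion on its own unit (extrapolation)**

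- Yield so far: 15/101 = 14.9%.
- Screened patients implied by 30 enrolments: 30 / (15/101) = 202.
- If exactly half of the apparently eligible patients were screened, the denominator would be 202 / 0.5 = 404. This is not a figure in the article.
- 95% half-width at 50%: 1.96 × √(0.25/N) = 4.9 points for N = 404, and 6.9 points for N = 202.
- True rate at which a test against 50% has 80% power (normal approximation, one-sided to two-sided 5%): about 56% to 57% for N = 404, and 59% to 60% for N = 202.

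These figures are far from those for n = 30, so the choice of unit matters.

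**4. What 30 participants do determine**

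Clopper-Pearson 95% intervals at the thresholds:

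- Tolerability, 21/30 = 70%: 51% to 85%.
- 1-month response, 24/30 = 80%: 61% to 92%. If only the 25 completers are counted, 20/25 = 80%: 59% to 93%.
- Retention at 70% is defined only for Winnipeg residents. Its denominator is at most 30 and not given, so if some participants live elsewhere its interval is wider than that for 21/30.

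**The case against.** The strongest reply is that nothing has been shown to be miscalculated. About 80% does arise at n = 30 for plausible pairs, such as 50% against 75% at two-sided 5%, or 25% against 50%. The sentence carries a citation that was not available for this review. A journal article may leave null, alternative and alpha to a fuller document. A threshold that must be met is also a decision rule, and a pass probability can attach to it.

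Much of this stands. A reader might infer that the 80% is an arithmetic error, or that true power is 29%. The documents support neither, because the 29% depends on a null, an alpha and a true rate that this review assumed. The absence of null and alpha is not by itself a fault in an article, and it can be said only that no test is stated here, not that none exists. The accrual target also affects the criterion indirectly, since enrolling 30 determines roughly how many patients are screened.

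What does not stand is the attachment of the figure to 30 enrolled people. A separate plan could add a test, but neither it nor the cited source could make 30 the denominator of the criterion as this article defines it. The indirect link through accrual is not set out in the article and would lead to a different number of units.

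A reader might also infer that a target of 30 is unjustified. That goes too far, because the pilot precedent and the descriptive aims do not depend on the power sentence, which is introduced as an additional reason.

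**Conclusion.** The claim of 80% power is unsupported by the design as described. It uses enrolled participants for a proportion defined on apparently eligible patients, and the article plans only a descriptive comparison of that proportion with 50%. This is an internal inconsistency of moderate importance. No threshold, analysis or progression rule changes as a result, and 30 may still be a reasonable size for a feasibility study.

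The conclusion about the unit needs no numerical assumption; it follows from the article's own definition. The power figures at n = 30 rest on assumed rates and alphas and show only how far the answer moves. The figures at 202 and 404 rest on the recruitment yield to March 2025 continuing and, for 404, on half of apparently eligible patients being screened. The participant-based intervals assume independent participants and results exactly at the thresholds.

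**What to change.** Delete the power sentence. Alternatively, restate it for the criterion as defined, giving the expected number of apparently eligible patients as denominator, with null rate, alternative rate and alpha.

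In either case:

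- Report screening coverage with a 95% confidence interval on the count of apparently eligible patients.
- Support the sample size by the precision of the participant-based criteria: tolerability at n = 30 (21/30: 51% to 85%) and 1-month response (24/30: 61% to 92%).
- Compute retention on the Winnipeg-resident subset and say that its interval will be wider.

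The cost is a few sentences and a sample-size rationale that reads slightly less favourably. No extra participants or data are required beyond a count of apparently eligible patients, which the criterion already needs.

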#### VR Intervention Procedures

Similar procedures to phase 3 will be used in phase 4A, with 3 exceptions made in accordance with preliminary phase 3 data. First, following baseline measure administration, the research assistant will administer a brief video via laptop that introduces the participant to the VR-GMI program, including how to operate the controls and put on the headset. The video (rather than verbal instruction) serves to standardize study expectations and technical knowledge across participants. Second, new measures have been introduced in addition to the measures used in phase 3. The first time a participant completes a stage, they will be administered the Theoretical Framework of Acceptability Questionnaire, which consists of 7 items rated on a 7-point Likert scale inquiring about the acceptability of a behavioral intervention [54] (Figure 4). In addition, following the limb simulation stage (both with and without leg tracking), each participant will be administered the Virtual Embodiment Questionnaire, a validated measure for agency and ownership in a virtual experience involving avatar embodiment [55]. Finally, the Brief Pain Inventory and Patient Reported Outcomes Measurement Information System will be verbally administered over the phone 1 month following each participant’s final VR session to measure PLP intensity and interference, respectively, through validated self-report measures [56-58].

The last and most significant amendment made between phases 3 and 4A is the administration of the VR-GMI program in the home setting following hospital discharge. Data from phase 3 suggested that participants were discharged from the hospital before 2 weeks had passed, which prevented them from receiving the VR dose necessary to see a treatment effect [23]. Therefore, a research assistant will contact participants over the phone following their discharge to inquire about their interest in continuing participation for the remaining sessions in their home. If they wish to continue (and they live in Winnipeg), their participation will proceed with home visits. If they do not reside in Winnipeg, their participation will be discontinued by the researcher; however, their willingness to continue the program will be recorded. Participants will be allowed to continue the VR-GMI program for up to 17 days to analyze long-term acceptability and dosage effects. Immediately following the completion of the feasibility trial, relevant modifications will be made to the prototype based on results.

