## Introduction

### Literature Review

More than 7000 lower limb amputations (LLAs) are performed in Canada each year due to (in order of decreasing prevalence) diabetic, vascular, traumatic, cancerous, and congenital indications [1]. Approximately 70% of these individuals will develop phantom limb pain (PLP) [2,3], a type of neuropathic pain where one experiences uncomfortable kinesthetic or somatosensory sensations in their missing limb following amputation [4]. PLP can be experienced for the first time within days following amputation (if not, within 1 year) and persists to variable degrees of intensity over a lifetime depending on the individual [5]. Research suggests that PLP is more likely to occur in people with more recent amputations compared to those who underwent amputations further in the past [2,3]. In addition, those who have an amputation due to chronic conditions (eg, vascular disease or diabetes mellitus) may have worse outcomes than those who undergo traumatic amputations because of preoperative factors (eg, preamputation pain) [2]. While PLP may improve over time if untreated, the lack of PLP treatment most often can significantly reduce quality of life, both psychologically and physically [6,7]. For example, research suggests PLP reduces mobility, which has adverse effects on independence (such as maintaining employment) and social role fulfillment [6,7]. PLP has also been implicated in a variety of other negative sequelae, including poorer sleep quality and increased depressive or anxious symptomatology [8-10]. The high prevalence of PLP among the growing number of LLAs, coupled with a lack of outpatient support, reflects an urgent need to develop effective treatments tailored to address the gap in care between the inpatient and outpatient settings to mitigate these negative sequelae.

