However, each phase of the protocol also presents limitations. The feedback collected in phase 1 was collected informally through open-ended questions; therefore, the resulting recommendations were the result of simple compilation rather than systematic analysis. Furthermore, due to the COVID-19 pandemic, only 2 study partners with lived PLP experience were available to trial the VR prototype in person (all were able to observe video developments). Furthermore, although the initial goal was to recruit 5 diverse partners with lived PLP experience, only 3 were consulted. Meanwhile, phase 2 recruitment was completed via convenience sampling and was limited to interested individuals able to attend at the NRC building. Thus, the results of phase 2 likely do not capture the barriers encountered by the diverse population undergoing LLAs in Canada. Phases 3 and 4 have and will encounter similar bias. While a more representative sample may be recruited at the outset, data from phase 3 suggest participants are discharged from the hospital before completing the VR program for the recommended treatment period. Because only individuals who live in Winnipeg may logistically continue the program after discharge, people who live in rural or Northern communities are unlikely to receive the VR dosage necessary to demonstrate a treatment effect. This exclusion limits generalizability to Indigenous peoples living in Northern communities, who are disproportionately affected by diabetic LLA [65]. These limitations highlight that, while we can use the data of this protocol to inform VR development, more representative recruitment will be necessary before the clinical feasibility of the program for the general population can be ascertained.

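### Phase 4A sets length of engagement partly by place of residence, so the dose-PLP association is open to confounding of unknown direction and size

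*Protocol article*

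**What the plan says.** The phase 4A section on VR Intervention Procedures sets two routes after discharge. For residents: "If they wish to continue (and they live in Winnipeg), their participation will proceed with home visits". For others: "If they do not reside in Winnipeg, their participation will be discontinued by the researcher", with only their willingness to go on recorded. The upper limit and its purpose are also stated: "Participants will be allowed to continue the VR-GMI program for up to 17 days to analyze long-term acceptability and dosage effects". Home visits were added because, in phase 3, "participants were discharged from the hospital before 2 weeks had passed".

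Pilot Outcomes gives a directional hypothesis: "Participants who spend an extended amount of time in the VR-GMI program will report lower PLP incidence", with lower intensity and interference where PLP has already begun.

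For this objective, Data Analysis plans scatterplots to "explore the association between the length of program engagement and the Brief Pain Inventory" or the pain interference score, a mean or median difference in engagement between participants with and without PLP onset, and, if appropriate, regression of PLP outcomes on VR dosage. It names no split or covariate for residence. The same section does confine the retention criterion to Winnipeg residents. The follow-up call, one month after the last session, carries no residence limit.

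Strengths and Limitations accepts that rural and Northern participants will probably receive too little VR, and treats this as a limit on generalizability. It adds that Indigenous peoples in Northern communities are a group "who are disproportionately affected by diabetic LLA". The Literature Review says that people whose amputation follows a chronic condition "may have worse outcomes than those who undergo traumatic amputations because of preoperative factors".

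**The concern.** Length of engagement is the exposure in objective 3. For a non-resident it ends at discharge by rule; for a resident it can run on for as long as the participant is willing, up to the common limit. A plot of PLP against engagement therefore partly compares Winnipeg participants with others. Any difference in prognosis between those groups enters the slope, whether it comes from indication, care or anything else linked to residence.

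The article discusses residence only as a question of whom the results apply to. It is also a question of whether the association can be read as dosage at all. The article says that the 17 days serve to examine dosage effects, and phase 4A precedes a randomized trial, so a reader could take a slope in the predicted direction as an early dose signal.

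**Working it through.** The plan gives no figure for this association, so there is none to reproduce. The check has four steps.

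**1. Does the rule bind?** Sessions are daily, up to 17 days, and phase 3 stays ended before 14 days. If phase 4A stays are similar, a non-resident loses more than 17 - 14 = 3 available days. A non-resident with a long stay can still reach day 17.

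**2. Closed form with no VR effect.** All inputs are assumptions: share outside Winnipeg p = 0.4; mean dose 7 versus 15 sessions; within-group dose SD 3; PLP SD 2.5; PLP higher by d points outside Winnipeg.

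- Dose variance = 3² + p(1 - p) × 8² = 9 + 0.24 × 64 = 24.36.
- Covariance = -0.24 × 8 × d = -1.92d.
- d = 1: slope -1.92/24.36 = -0.079 per session, or -1.3 points over 17 sessions; r about -0.15.
- d = 2: slope -3.84/24.36 = -0.158 per session, or -2.7 points over 17 sessions; r about -0.29.
- With a dose gap of 5 sessions and d = 1: -(0.24 × 5)/(9 + 0.24 × 25) = -1.2/15 = -0.08 per session.

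The value of d decides the result. If it arises only through indication, it equals the difference in chronic-indication share times the effect of indication on PLP. With an assumed 20-percentage-point difference and a 2-point effect, d = 0.2 × 2 = 0.4. The first set of inputs then gives -0.768/24.36 = -0.032 per session, about -0.5 points over 17 sessions, r about -0.06.

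**3. Simulation with no VR effect.** 4,000 runs per scenario, n = 25, the completers the article expects. Assumed: mean stay 9 days, 70% of residents continuing to day 17, 85% daily compliance, PLP SD 2.5. The rule alone produced a gap of about 5 sessions when both groups had the same mean stay. The last column is the share of runs in which a one-sided 5% test showed benefit. It is a yardstick only; the plan announces no such test.

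| Scenario | Unadjusted slope per 10 sessions | Apparent benefit |
|---|---|---|
| No prognostic gap, 20-50% non-resident | about 0 | 4-5% |
| Non-residents 1 point worse, 20-50% | -0.6 to -0.7 | 11-14% |
| Non-residents 2 points worse, 20-50% | -1.2 to -1.5 | 20-30% |
| 1 point worse, and PLP 1 point higher per 4.5 extra days of stay, 40% | +0.28 | 3% |
| Non-residents 1 point better, 40% | +0.73 | 1.5% |
| 1 point worse, non-resident stay averaging 20 days (dose gap 0.4), 40% | -0.12 | 6% |
| No gap, PLP falling 0.03-0.05 points per day, 40% | -0.35 to -0.60 | 9-13% |

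The last row reflects follow-up timed from the final session: participants stopped at discharge are assessed sooner after surgery. For PLP incidence the same timing leaves less time for onset and pulls the other way.

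**4. What a residence term does.** In the first three scenarios it brings the slope to between -0.04 and +0.08 per 10 sessions and the rate to 4-6%. It does not correct the timing scenario (-0.34 to -0.63). In the length-of-stay scenario it moves the slope from +0.28 to +1.65, because the remaining dose variation then carries the stay effect. Adjustment removes confounding by residence and nothing else.

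**The case against.** The strongest reply is that little rests on this analysis. No progression criterion uses the dose-PLP association, the regression is conditional, and the article calls its aims descriptive and exploratory. Exploratory Outcomes already asks whether PLP varies with sociodemographic variables and indication, and covariates for an optional model are commonly left to an analysis plan. Most of this stands, and it keeps the point modest. It does not remove it: the exploratory objective examines those variables separately from dose, while the protocol itself contains the rule that sets dose by residence and describes the regression as one of dosage effect.

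A reader might go further and infer that the analysis is tilted toward the hypothesised benefit, by 1 to 3 points. The article does not support that. Its remark on diabetic amputation concerns Indigenous peoples in Northern communities, not everyone outside Winnipeg. Its remark on chronic conditions says only that outcomes may be worse, and it ranks diabetic and vascular causes as the commonest overall, so many Winnipeg participants probably share them. If longer stay marks worse PLP, the slope can turn positive.

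A reader might also want the main analysis restricted to Winnipeg residents. That is a debatable trade. It discards the dose variation set by the rule and keeps the part that depends on willingness and tolerance. With an assumed 40% non-resident share, it leaves 25 × 0.6 = 15 people.

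**Conclusion.** The point holds in a limited form. Residence partly determines length of engagement by rule, and the plan relates engagement to PLP without separating or adjusting for residence. The pooled association is therefore open to confounding by residence and by factors linked to it, such as indication.

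Direction and size are unknown. A tilt toward apparent benefit is plausible from the article's own remarks but not shown. Under assumed inputs and no VR effect, the slope ran from -1.5 to +0.73 points per 10 sessions, and was about 0 when the residence groups had the same prognosis. The share of non-residents, their prognosis and their stay are not given, so none of these values is an estimate for this study. The consequence is a limit on what can be said about dosage; the feasibility criteria are unaffected.

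**What to change.** In the phase 4A Data Analysis section, for objective 3:

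- mark Winnipeg and non-Winnipeg participants separately in the scatterplots;
- report the engagement difference by PLP onset overall and by residence;
- include residence and, as far as the sample allows, amputation indication in any dose regression, with the unadjusted result alongside;
- state that the pooled association is not interpreted as a dosage effect, because the researcher ends exposure for non-residents at discharge.

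Residence and etiology are in the phase 3 baseline questionnaire, whose measures phase 4A retains, so no new data are needed. The cost is wording and slightly less precision in an exploratory analysis of about 25 participants. No change to the discontinuation rule is proposed.
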